## 10. HUMAN SUBJECTS

Overall we expect to consent 350 child/parent dyads and have at least 160 child/parent dyads get randomized to treatment who meet the following eligibility criteria. Research involving pediatric obesity interventions typically have a large number of female participants (60%) compared to male participants. Based on previous pilot work completed for overweight/obese children age 4-12 years, more than 70% were female. Therefore, we expect that at least 60% of the participants will be female and 40% male. Our goal will also be to obtain a racial/ethnic breakdown of participants that is similar to that of San Diego County. San Diego encompasses a wide range of ethnically diverse individuals, including 52.9% white non-Hispanic, 27.9% Hispanic, 11.1% Asian-American, 4.7% African-American 1.6% American Indian and Alaska Native, 0.5% Native Hawaiian or Pacific Islander. Considering these statistics, we expect that we will obtain an ethnically diverse sample of San Diegan children.

Inclusion criteria are: a) An overweight child age 7-12, whose BMI is  $\geq 85^{\text{th}}$  percentile but  $<99.9^{\text{th}}$  percentile for age and gender; b) The parent willing to participate and can read English at a minimum of a 5th grade level; c) Parent and Child willing to commit to attending all treatment and assessment sessions and be randomized to either treatment arm; d) Child, parent, and 1st degree relatives are free from psychiatric illness than may affect participation; e) Child does not have any medical conditions that impact weight or may affect participation in physical activity or treatment f) Child is not taking medications that may impact their weight (unless medication dosage is stable and not for the purpose of impacting weight and appetite).

Exclusion criteria include: 1) Children with serious medical conditions that affect their weight; 2) Children taking medication that affect appetite or weight; 3) Children with severe developmental delay or disability that would affect participation; 4) Children or parents with psychological illness that would limit treatment participation; 5) Families who will move out of the area within the time frame of the study.

Prior to inclusion, parents and children will be weighed and measured and BMI calculated to determine if they are eligible for participation. Children must have a BMI percentile that is  $\geq 85^{\text{th}}$  percentile, according to the CDC criteria for age and gender. Parents must have a BMI  $\geq 25$  to qualify.

## 11. RECRUITMENT

All advertisements for the intervention will target families with at least one child who they think is overweight/obese in the target age range. Advertisements will state that this is a *family* weight loss program intended to make lifestyle changes that will benefit the whole family. Both parent and child must agree to participate in the study. Children who state that they are not interested in participating in the program will not be enrolled, as well as their parents.

Families will be recruited through advertisements placed in local newspapers, radio, family newsletters, TV ads, ResearchMatch, clinicaltrials.gov, and the internet. If needed, information for direct mailing/emailing will be purchased from companies or services such as the U.S. Postal Service that allow you to purchase/ pay to send mail or email to individuals. Families will also be recruited from Rady Children's Hospital potentially through the use of electronic medical records (EPIC system). A request for partial waiver of HIPAA authorization for recruitment purposes has been submitted and additional approval will be obtained from this institution in order to do so. Additional flyers and posters will be placed in pediatricians' offices, community centers, and schools. We will also recruit potential participants through a "snowball recruitment" effort. This effort would involve current participants in our study (either in the treatment or follow-up phase of the study). These current participants will be asked to refer other potential families that they think would be interested in our study. They will be given previously approved recruitment flyers to give to these new potential families. They will not be compensated for these recruitment efforts or given preferential treatment during the intervention because of these efforts.

For our study, our recruitment staff will use our IRB approved ads and text, landing pages, and online screens to advertise. Our recruitment staff may advertise on Facebook, Google, Instagram, medical informational sites, and other relevant app networks. The ads will target adult parents over the age of 18 with the advertisements in the San Diego area. Once someone responds to an ad, they will be directed to our landing page with information about the study. The language on this landing page is the exact language on our current IRB approved landing page. Interested parents can complete a prescreener that is embedded directly on the landing page with their name, email, phone number, a best time to call, and information that will help us

determine the child's age, home zip code, and BMI percentile to assess basic eligibility for this study. This will register their interest in this study. The information will be sent from a secured webpage hosted by a secure server, through a secured email to a UCSD email address that is only accessed by approved study personnel through a secure UCSD login. Only approved study personnel within the lab will have permission to access provided information so that we may move forward with the screening process.

Participants who respond to all recruitment efforts, including social media advertisements, will be asked to complete an initial online screen to determine initial eligibility. If individuals do not have online access or do not wish to complete the screen online, they can complete an extended screening call that will include these questions as part of the telephone screen. Participants who meet study inclusion criteria will then complete a phone screen to further assess eligibility.

We are requesting a Waiver of Documented Consent for the phone screen because this process meets criteria for minimal risk to the subject. We will ask the participants if they are willing to answer additional screening questions over the phone and obtain verbal consent for this process. This component is minimal risk to the participants because: 1) the waiver will not adversely affect the rights or welfare of the subjects; 2) this component could not be practicably carried out with the waiver; 3) there are no additional risks outside the usual scope of practice in answering these questions; and 4) pertinent information will be provided to the subjects after participation.

If participants meet initial screening criteria, they will be scheduled for an orientation to learn more about the study, review the informed consent and have all questions answered. If they remain interested in participating, they will then sign an informed consent and be scheduled for the first assessment.

## **12. INFORMED CONSENT**

The online screening will assess for basic inclusion and exclusionary criteria. This process presents no more than minimal risk of harm to subjects, and involves no procedures for which written consent is normally required outside of the research context. For these reasons, we request a waiver of documented consent for the online screening. For individuals who do not have online access, the questions asked on the online screen will be administered over the phone in conjunction with the phone screen.

The phone screening will assess for basic inclusion and exclusionary criteria. This process presents no more than minimal risk of harm to participants and involves no procedures for which written consent is normally required outside of the research context. For these reasons, we request a waiver of documented consent for the phone screen.

Those families who appear to be eligible will be invited to the research office or remotely via Zoom for orientation during which time a more complete description regarding the purpose of the research, the timeline and procedures of the study, the risks and benefits, and how confidentiality will be maintained will be provided. Family members will be given an opportunity to ask questions at this time and informed that participation is voluntary and that they can withdraw from the study at any time. The orientation and consent process may take place with a group of potential participants. Participants may ask questions as a group and they will also be informed that they will each have an opportunity to privately ask additional questions. If individuals are unsure as to whether they are willing to participate in the study, they may take the consent form home with them. If they later decide they wish to participate, they may schedule their first assessment and sign the consent form prior to participating in the assessment.

Families who are eligible and agree to participate in the study will then provide parental informed consent and child assent that has been approved by the Institutional Review Board of UCSD after the orientation session. Consent will be obtained by one of the study investigators or the program coordinator. All consenters have or will have completed HIPAA training prior to obtaining consent. At this time, only families comfortable communicating, reading, and writing in English will be enrolled in the study.

For those who are consented in a zoom meeting, we will require a waiver of written consent. During the zoom call, the study staff member responsible for obtaining verbal consent will review the emailed document with the

participant. The study staff member will provide an opportunity for the potential participant to ask questions. When all of the potential participant's questions have been answered, the study staff member will ask the participant if they are ready to provide consent and then verbal consent will be obtained. Should the potential participant desire more time to make a decision to participate, they will be provided information on how to reschedule their zoom verbal consent call. Justification for this oral consent procedure is that the research presents no more than minimal risk of harm to subjects and involves no procedures for which written consent is normally required outside of the research context.

Families who are enrolled in the main study and agree to participate in the optional additional assessments for the ancillary study will complete an additional parental informed consent.

An amendment on May 2, 2019 changed the length of storage for video data. In order to facilitate the re-consenting process for participants who have completed the study prior to the approval of the amendment, the study is requesting a waiver of documented consent for these participants. The study team will make several attempts to contact these study participants, first via phone (x2), then via email (x2), before a letter is sent to the family. These phone calls and emails will ask the family to contact the study team so we can inform them of the changes to the protocol and obtain verbal consent over the phone.

- The changes involve minimal risk to subjects, as they are limited to changes that impact the timeline pertaining to storage of data.
- The changes involve no procedures for which written consent is normally required outside of the research context.
- The verbal consent will be documented by the study team on the originally signed consent form and in a data sheet for tracking purposes. Standard note to file will be added to the subject's chart indicating the date which they agreed to the changes.

If a subject chooses not to agree to the extended storage timelines, the video data will be stored for the length of time to which the subject initially agreed.

In the event that no response is received for the request for consent for these changes in data storage timeline, the study is requesting a waiver of consent to allow for the extended storage of video data for subjects who completed the study prior to approval of the amendment that changed storage timelines.

- The changes to storage timelines represent minimal risk.
- The changes do not adversely impact the rights and welfare of subjects, as they previously agreed to storage of their videos and the amendment simply modifies the time frame. Appropriate confidentiality measures will still be in place to protect the data.
- The research could not practicably be carried out with the waiver because some of the families have completed the study and are no longer in contact with the study team.
- Whenever appropriate, the subjects will be provided with additional pertinent information after participation.

### **13. ALTERNATIVES TO STUDY PARTICIPATION**

Subjects can choose not to participate in the study at any time. There are no alternative therapies provided by the study. If the subject chooses not to participate, he/she can enroll in other clinical weight control programs offered in the area or at Rady Children's Hospital.

### **14. POTENTIAL RISKS**

During the program, participants will be asked to improve overall dietary intake and increase physical activity behaviors. Increasing the consumption of healthy foods while reducing high caloric foods may result in more than expected weight loss. Although increasing physical activity can have great benefits, participants may also experience some general fatigue or sore muscles or joints from being active. It is also possible that participants could fall or be injured in association with being physically active. Most of these injuries are not likely to require medical treatment. Performing moderate intensity physical activity such as walking reduces

the risk of these complications. There is no guarantee, however, that these complications will not happen to the parents and/or children.

Families may also be inconvenienced or frustrated by the assessment process. We will try to minimize any inconvenience for family members by scheduling assessments at their convenience and limiting the amount of time required for these assessments. Videotape family meals will occur in their home at their regularly scheduled mealtime to decrease any inconveniences and increase the validity of these assessments. Children may also become frustrated by or not like the intervention, surveys, or videotaped meals. Children who become frustrated or are experiencing extreme stress during the intervention or assessments will be allowed to stop and withdraw from the study without any consequence to themselves or their parents. Children may also feel uncomfortable being videotaped during assessments. However, most children become accustomed to being recorded after a few minutes.

Should a child or parent display symptoms indicative of physical or mental disorders during treatment, the interventionist will assess the problem, and in consultation with study supervisors, Drs. [name], [name], and [name], decide whether to withdraw the individual from treatment and/or to refer them for treatment elsewhere.

Safety of human participants is a major concern in a trial involving youth. The initial reporting of adverse events of any kind will take place with the study staff consulting with the PI. The PI will then decide whether the events are of such a severity that requires discontinuation of a particular treatment, and whether the participant should remain in the study or be withdrawn and referred elsewhere. In this study, adverse events will be defined as unanticipated problems involving risks to the study participant. A serious adverse event will be defined as any untoward occurrence that results in death; is life threatening; or creates persistent or significant physical or emotional disability. All such events will be immediately reported to the IRB.

Risk of loss of confidentiality: There is a small risk that confidentiality of survey data as well as other biological measurements will be lost or stolen during this study. However, the research team will make every effort to maintain this confidentiality (see details in Section 15). The nature of the genetic and microbiome information to be studied is also of low risk and has minimal chance to impact future employability, insurability, reputation, or other social factors. Disease specific markers will not be examined. The biologic information gathered in this study is for research only and will not be provided to the participant's physicians, insurers, or employers.

This intervention may also involve risks that are currently unforeseeable to us at this time. There is also a potential risk of loss of confidentiality, which is addressed in the following section.

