Confidentiality of participants will be protected in multiple ways. First, all participants will be given a unique identification number that will be used on all documents with no references to individual names, addresses, phone numbers or birthdays. Videotapes will also be given unique identification numbers and coders will be blinded to additional identifiers except for any names mentioned in the videotapes. Subjects may request that the taping be stopped or that part or all of the recording be erased at any time. Subjects may also view the recording prior to submitting it, and be allowed to not submit the data without any consequence to themselves. All data will be stored in locked file cabinets in locked rooms. The de-identified data will be entered into a password-protected computer that only the trained research staff, collaborators, and the PI will be able to access. All procedures will be approved by UCSD's Institutional Review Board to ensure that they meet standards for the protection of human subjects.

There is also the potential risk of loss of confidentiality. However, the research team will make every effort to keep all personal identifying information confidential. A unique identification number will be provided for each participant so that all data can be de-identified. Files linking names with subject ID numbers will be kept in a locked file that only the PI will have access to. All other data will be stored in locked cabinets in locked rooms in UCSD sponsored facilities or on a password protected computer that only the PI and RA will have access to.

[name] lab has well established protocols if a child or parent endorses anything that suggests abuse, neglect or harm to self or others. If any concerning statements are made at any time during the assessment of the family, or during the treatment of the family, Drs. [name], [name], or [name] will be immediately alerted and reviews statements made by the family with the staff member. All child abuse, harm, and neglect cases are reported to the state of California Child Protection Service, as required by the mandated reporting laws. Because of this low risk status, the data and safety monitoring plan (DSMP) for this trial focuses on close monitoring by the principal investigator (PI) in conjunction with a safety officer, along with prompt reporting of excessive adverse events and any serious adverse events to the NIH and to the IRB at the University of California San Diego.

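### Adverse events are limited to unanticipated problems, so the non-serious harms that the protocol itself foresees are not counted as adverse events

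*Protocol*

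**What the plan says.** Section 14 (Potential Risks) opens with harms that participation may bring. Dietary change "may result in more than expected weight loss". Being more active may cause tiredness and soreness, and "participants could fall or be injured in association with being physically active". Children may become frustrated or severely stressed by the sessions or assessments.

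Later in the section come the safety definitions. Staff first take adverse events, whatever their nature, to the principal investigator, who judges their severity and whether the participant should continue. Then: "In this study, adverse events will be defined as unanticipated problems involving risks to the study participant".

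Serious events are defined differently: "A serious adverse event will be defined as any untoward occurrence that results in death; is life threatening". The third and last criterion is an event that "creates persistent or significant physical or emotional disability". The next sentence reads "All such events will be immediately reported to the IRB".

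Section 15 (Risk Management Procedures and Adequacy of Resources) describes monitoring by the principal investigator together with a safety officer, and commits to "prompt reporting of excessive adverse events and any serious adverse events" to the NIH and the IRB. It also sets out what happens if weight loss is excessive: weekly weights, dietary advice, possible measurement at the research office with pediatric review, then notice to the child's own pediatrician and referral.

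**The concern.** A harm written into the protocol's list of risks is, in kind, anticipated. If adverse events are only unanticipated problems, a sprain, a minor fall, muscle soreness or a moderate excess of weight loss is excluded by definition. Yet in a behavioral weight-control program whose risks Section 18 calls minimal, these are the harms most likely to be seen.

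Two things depend on the definition. One is the step that brings events to the principal investigator. The other is the count behind the excessive-adverse-events trigger in Section 15. If foreseen events are not logged, that count omits them, and a later summary of adverse events by arm would omit them too. A statistical analysis plan cannot repair this, because it can only tabulate what staff were told to record.

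**Working it through.** No arithmetic applies. The protocol gives no expected event rate, no numerical threshold for what is excessive and no target for harms, so there is no figure to reproduce. The check sets the definitions against the risk list and the reporting triggers, one class of event at a time.

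**Inputs**
- Risk list: Section 14, opening paragraphs.
- Adverse-event definition, limited to the unanticipated: Section 14, "In this study, adverse events will be defined as unanticipated problems involving risks to the study participant".
- Serious-event definition, not limited to the unanticipated: Section 14, "A serious adverse event will be defined as any untoward occurrence that results in death; is life threatening" and "creates persistent or significant physical or emotional disability".
- Reporting triggers: Section 15, "prompt reporting of excessive adverse events and any serious adverse events".
- Separate route for weight loss: Section 15, first paragraph.

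**Classification, reading the wording literally**

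| Class of event | Adverse event? | Serious event? | Reaches a Section 15 trigger? |
|---|---|---|---|
| Unanticipated, not serious | Yes | No | Yes, counts towards excessive adverse events |
| Anticipated or not, meets a seriousness criterion | Not needed | Yes | Yes, as a serious event |
| Anticipated, not serious (minor fall, soreness, distress) | No | No | No |
| More weight loss than intended, not serious | No | No | No; handled clinically, with no NIH or IRB report stated |

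The last two rows are the gap.

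**Consistency within Section 14.** The instruction to bring all kinds of adverse event to the principal investigator comes shortly before the sentence that narrows the term. Under the first, a member of staff would report a sprain. Under the second, a sprain is not an adverse event. The protocol does not say which governs.

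**Consistency with Section 15.** To call a number of events excessive implies some level that was expected. That fits poorly with a category confined to events that nobody expected.

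**Immediate IRB reporting.** "All such events will be immediately reported to the IRB" follows directly on the serious-event definition. Whether it also covers adverse events is unclear, but on either reading it does not reach the last two rows.

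**The case against.** The strongest reply is that the protocol does not leave these harms unattended. Much of that stands, and it rules out several stronger readings.

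- **A reader might infer that foreseen harms can never be reported.** That is wrong. The serious-event definition covers any untoward occurrence that meets a criterion, anticipated or not, and Section 15 requires every serious event to be reported. A foreseen fall with a serious outcome is caught.
- **A reader might infer that a fracture leading to a hospital admission that resolves is neither an adverse event nor a serious one.** The documents do not establish this. The criterion is "creates persistent or significant physical or emotional disability", so a fracture might qualify as significant without being persistent. Section 14 also says that most activity injuries are unlikely to need medical care, so one leading to admission could be regarded as exceeding what was anticipated. What remains is that hospital admission is not mentioned, so its status is left to judgment.
- **A reader might infer that the safety officer would not see these events.** Section 15 does not limit the officer to events that meet the adverse-event definition, and it only summarizes the monitoring plan. What the officer receives is not stated.
- **A reader might infer that harms could not be compared between arms at all.** Section 9 provides for weights throughout treatment and for heights at mid-treatment, post-treatment and both follow-ups. Weight loss can be compared by arm from those data without any adverse-event label. The difficulty is with harms that have no other record, such as minor injuries.
- **A reader might put the loss at every event of the listed types.** That only restates the definition as a proportion, and it fails for serious events.

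The clinical routes are real. Excessive weight loss has its own procedure, staff are trained to respond to distress, and symptoms of physical or mental disorder are taken to study supervisors. None of these provisions states that the event is recorded as an adverse event or counted towards the NIH and IRB trigger. They answer the charge of neglect but leave the counting problem in place.

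**Conclusion.** The point holds in limited form. Under the definition in Section 14, foreseen non-serious harms are not adverse events, so they do not count towards the excessive-adverse-events trigger in Section 15. The definition also conflicts with the broader instruction to staff earlier in Section 14. This is a stated rule that yields a wrong count, and so is more than detail left for a later document.

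The size can be given only as a class of events: those foreseen in Section 14 and below the seriousness criteria. No rate or number can be attached to it. Serious events are unaffected, and excessive weight loss is still managed clinically.

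The conclusion rests on two assumptions. The first is that staff apply the definition as written; if they record every untoward event in practice, the gap is one of wording. The second is that the full monitoring plan does not set a broader definition that overrides the protocol's.

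**What to change.** Reconcile Sections 14 and 15 as follows.

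1. Define an adverse event as any untoward occurrence in a child or parent during participation, whether or not it was anticipated.
2. Keep the unanticipated problem as a separate category for IRB reporting, so that the existing wording still has a use.
3. State that events of the kinds listed in Section 14, including weight loss handled under Section 15, are logged as adverse events and count towards the Section 15 trigger.
4. Log events in the same way in both arms, at the weekly treatment sessions and at the scheduled post-treatment and follow-up assessments, so that they can be summarized by arm.
5. State whether an event that leads to hospital admission and then resolves counts as serious. This is a secondary clarification, and the main point does not depend on it.

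These changes affect definitions and recording only and alter no treatment or clinical rule. The cost is a modest amount of extra recording and a larger number of reported adverse events, most of them probably minor. After treatment the scheduled assessments are six months apart, so minor events in that period will be recalled less completely than those logged weekly. The summary should separate the two periods.

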## **15. RISK MANAGEMENT PROCEDURES AND ADEQUACY OF RESOURCES**

All parents will be advised about healthy eating and activity practices including dietary changes and increasing physical activity/decreasing sedentary behaviors in the group meeting. Parents will be advised to gradually make changes in these behaviors. The child and parent's weight will be monitored weekly. However, parents may report excessive weight loss in themselves or their children. If this occurs, an increase in caloric intake or encouragement of healthier, alternative practices will be made. Children may be asked to come to the research office so that weight and height can be measured by research staff and discussed with myself, a board certified pediatrician. If unhealthy practices or significant weight loss continues, the child's pediatrician will be notified and referrals for other treatment made.

Participants will also receive a thorough introduction to the study questionnaires, assessment tasks, and videotaped family meal preparing them for the nature of the questions/activities. Such preparation often decreases the risk of becoming unduly distressed. If a participant does become distressed, study staff will be trained to respond in a supportive, empathic way and to give the subject the opportunity to take a break. The intervention materials will address how to lose weight and develop healthy eating and activity habits, which is generally considered healthful. The consent process will be discussed with the participants, and they will be assured of the confidentiality of their responses.

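### Adverse events are limited to unanticipated problems, so non-serious harms the protocol foresees, chiefly falls, injuries, soreness and fatigue, stay out of the monitored count

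*Protocol*

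**What the plan says.** Section 14 (Potential Risks) gives the protocol's only definition of an adverse event: "adverse events will be defined as unanticipated problems involving risks to the study participant". It defines a serious adverse event separately, as any untoward event with a fatal, life-threatening or lastingly or significantly disabling outcome. That definition does not require the event to be unanticipated, and such events go to the IRB at once.

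Earlier in the same section the protocol names the harms it expects might occur:

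- Weight: "Increasing the consumption of healthy foods while reducing high caloric foods may result in more than expected weight loss".
- Fatigue and soreness: "participants may also experience some general fatigue or sore muscles or joints from being active".
- Falls and injuries: "It is also possible that participants could fall or be injured in association with being physically active".
- Frustration and stress: "Children who become frustrated or are experiencing extreme stress during the intervention or assessments will be allowed to stop and withdraw from the study".

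Section 15 (Risk Management Procedures and Adequacy of Resources) adds a staff response to distress: "If a participant does become distressed, study staff will be trained to respond in a supportive, empathic way". It then describes the data and safety monitoring plan as close oversight by the principal investigator with a safety officer, together with "prompt reporting of excessive adverse events and any serious adverse events to the NIH" and to the IRB.

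**The concern.** An adverse event is ordinarily any untoward occurrence, with unanticipated problems forming a smaller group that has its own reporting route. Here the smaller group has become the whole definition. The harms most likely to arise from asking children aged 7 to 12 and their parents to eat less and move more are the ones the protocol lists in advance, and the definition leaves them out unless they are grave.

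At stake is what the principal investigator and safety officer can count. If non-serious injuries were more frequent in one arm, that excess would not appear in the event stream they are asked to watch. Nor could it be recovered at analysis, because staff following the definition would have had no reason to record those events.

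**Working it through.** No arithmetic applies. The point turns on a definition, and the protocol gives no event rates. The check sets the definition against each foreseen harm and asks which planned record would hold it.

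**Step 1. Which harms are anticipated?** Section 14 lists harms by type, then says separately that there may be risks that cannot be foreseen at present. The document thus draws its own line between foreseen and unforeseen harms, and the listed types fall on the foreseen side.

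**Step 2. Where would each listed harm be recorded?**

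| Foreseen harm | Adverse event if non-serious? | Serious event if grave? | Other planned data, both arms |
|---|---|---|---|
| Excess weight loss | No | Yes | Weekly weights (Section 15); height and weight at all four time points (Table 1) |
| Frustration, stress, distress | No | Yes | Drop-out; Child Behavior Checklist and Pediatric Quality of Life Inventory at all four time points (Table 1) |
| Fatigue, sore muscles or joints | No | Yes | No event record |
| Falls and injuries | No | Yes | No event record |

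Section 9 refers to Table 1 for the full list of measures. That table has rows for attendance, self-monitoring, adherence, drop-out and satisfaction, and none for injuries or adverse events. For the last two rows above, the adverse event stream is the only planned place for an event record, and the definition closes it.

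For the first two rows the data exist, but as measurements at set times or as withdrawals. They are not event records and do not feed the adverse event count.

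**Step 3. Does the definition fit the serious category?** Take a fall during exercise that causes lasting disability. It is foreseen by type, so it is not an adverse event under Section 14. It has a grave outcome, so it is a serious adverse event under the same section. A serious adverse event that is not an adverse event shows that the two definitions do not nest.

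**Step 4. Does the definition fit the monitoring plan?** Section 15 has two streams: excessive adverse events, and any serious adverse event. Grave foreseen harms reach the second stream. Non-serious foreseen harms reach neither.

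**The case against.** The strongest case on the other side has five parts.

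- *Sections 14 and 15 can both be followed.* A reader might infer that the definition and the monitoring rule contradict each other. They do not strictly do so, because an excess of unanticipated problems is a coherent trigger. This stands: the two are poorly matched, not contradictory.
- *Much is captured elsewhere.* A reader might infer that no foreseen harm can be seen or compared between FBT+PT and FBT. The documents do not support that. Child BMI z-score is the primary outcome, drop-out is compared by survival analysis (Section 9, Analysis), psychosocial scales are repeated, and grave harms are reported as serious events. This also stands, and it narrows the point to non-serious events, chiefly physical ones. The protocol itself expects most activity injuries not to need medical treatment.
- *The intent may be broader.* Section 14 speaks of adverse events of any kind being raised with the principal investigator, and the word unanticipated is not defined. An injury well beyond what the section describes might be treated as unanticipated. This is fair, but the phrase uses a term that the same paragraph then defines narrowly. If the intent is broader, the definition should say so.
- *Listed harms are managed clinically.* Excess weight loss, distress and signs of physical or mental disorder each have a response path in Sections 14 and 15. That is true and is not criticised here. None of those paths says that the case is recorded as an adverse event.
- *The monitoring plan is only summarised.* Logging details may sit in a fuller document. They may, but the narrow definition is stated here for the whole study and would govern any log built on it.

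**Conclusion.** The point holds in a limited form. The adverse event definition in Section 14 leaves out non-serious harms that the same section foresees, so they do not enter the excessive adverse event stream in Section 15. It is also narrower than the serious adverse event definition beside it. The effective gap is falls, injuries, soreness and fatigue that are not serious. For excess weight loss and stress, what is lost is the event record, not the underlying data.

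A reader might go on to infer that the trial will record almost no adverse events and that a near-empty table will pass as evidence of safety. The documents give no rates, describe no adverse event table and make no such claim, so that remains conjecture.

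The conclusion rests on two assumptions: that staff apply the definition as written, and that a harm type listed in advance counts as anticipated. It does not depend on matters a statistical analysis plan would normally settle, since no analysis can recover events that were never recorded.

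**What to change.** Reconcile the definition in Section 14 with the risk list in that section and the monitoring plan in Section 15:

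- Define an adverse event as any untoward physical or psychological occurrence in the child or parent during participation, whether or not it was anticipated or is thought to be related to the study.
- Keep unanticipated problem as a named subset with its own IRB reporting. The serious category then sits inside the adverse event category.
- Log events in the same way in both arms at contacts that already take place, namely the 20 weekly sessions and the assessments, so that ascertainment does not differ by arm.
- Tabulate the events by arm for the principal investigator and the safety officer.

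The cost is an amendment of one sentence, a short log form and a little staff time. The count of minor events will rise, and reviewers of the table should expect that.
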